# Efficacy of acupuncture in the treatment of asthenospermia in obese men: study protocol for a randomized control trial

**DOI:** 10.3389/fmed.2026.1749806

**Published:** 2026-03-11

**Keywords:** acupoint, acupuncture, asthenospermia, male infertility, obesity

## Abstract

**Background:**

Asthenospermia is one of the most common causes of male infertility. In recent years, with changes in dietary habits, the number of obese patients with asthenospermia has been increasing, leading to a decline in male fertility. However, there remains a lack of safe and effective treatments for this condition.

**Objective:**

This study aims to confirm the efficacy and safety of acupuncture in obese patients with asthenospermia.

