**Results:**

This study is expected to demonstrate whether acupuncture is effective and safe in the treatment of asthenospermia in obese men.

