### Study design and settings

2.1

Our study is a 1:1 randomized controlled trial with two parallel groups and will be reported in accordance with the Standards for Reporting Interventions in Clinical Trials of Acupuncture and the SPIRIT 2013 Statement (19, 20). A total of 72 participants will be recruited for this study, with 36 participants assigned to each group. All participants will receive a course of acupuncture treatment after being informed about the study, risks, and benefits, and after signing an informed consent form. The trial flow chart and time point of the assessment are shown in Figure 1 and Table 1.

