#### Blinding

2.2.8

In this study, the acupuncture practitioners will be not blinded, while the participants, outcome data collectors, statistical analysts, and outcome assessors will be blinded. Both the acupuncture group and the sham acupuncture group underwent skin penetration, but the location and depth of the acupuncture will be different. Participants will be in separate rooms, positioned supine for acupoint selection, with curtains drawn below the head to obstruct their view of the specific acupuncture locations. Additionally, appointments will be scheduled for the acupuncture sessions to prevent conversations among the participants.

Participants will be informed prior to randomization: You have a 50% chance of being assigned to either the traditional acupuncture group (deeper needle insertion) or the modern acupuncture group (shallow needle insertion). After the final treatment session at Week 12, each participant will complete a questionnaire asking, “Did you receive traditional acupuncture?” with response options of “Yes,” “No,” or “Uncertain.” Ultimately, Bang’s blinding index and James’s blinding index will be used to assess whether participants could distinguish between receiving real acupuncture or sham acupuncture (23, 24).

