#### Sham acupuncture group

2.3.3

The procedure for sham acupuncture will adhere to the protocol outlined in our previous article (25, 26). Participants will assume a supine posture and undergo standard localized disinfection. Subsequently, the 0.3 mm × 25 mm stainless steel milli-needle (Huacheng Brand, Beijing Keyuanda Medical Devices Co., Ltd.) will be inserted at the acupoint without deqi sensation. Both needle retention time and the overall treatment period will match those applied in the acupuncture group. Specific manipulations will be performed by the acupuncturist: 10 mm lateral to the ST36 (Zusanli), 2–3 mm straight stab; 10 mm anterolateral to the SP6 (Sanyinjiao), 2–3 mm straight stab; 10 mm posterior to the KI3 (Taixi), 2–3 mm straight stab; 5 mm lateral to the KI12 (Dahe), 2–3 mm straight stab; 15 mm lateral to the CV3 (Zhongji), 2–3 mm straight stab; and 15 mm lateral to the CV4 (Guanyuan), 2–3 mm straight stab (Figure 2).

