#### Data analysis

2.5.2

Statistical analysis will be performed using SPSS (Chicago, IL, USA). For quantitative data (e.g., PR, sperm concentration, semen volume), normality of distribution will be first assessed. For data meeting normality, descriptive statistics will be presented as mean ± standard deviation. Non-parametric rank-sum tests will be used for non-normally distributed data. Count data will be expressed as frequency and percentage [*n* (%)]. For unordered categorical data, chi-square tests will be applied; for ordered categorical data, non-parametric rank-sum tests will be selected. The test level will be set at α = 0.05. *P* < 0.05 indicated statistically significant differences. For repeated measures data, repeated measures analysis of variance (ANOVA) will be performed. If the sphericity test is not satisfied, the results from the Greenhouse–Geisser correction in one-way ANOVA will be used.

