### Quality control

2.6

All relevant personnel will participate will attend specific training about the study objectives, protocol of intervention strategies, and quality control before the study so as to make them understand the protocol and be consistent in the interventions and evaluations during the study process. Before the trial commencement, two TCM practitioners from the selected department will undergo acupuncture technique training. Subsequent interventions will be performed by these two practitioners. The quality control officer will be responsible for establishing the treatment control and quality assurance system for the clinical study. They shall accurately, thoroughly, and meticulously document study case details according to case report form requirements, ensuring content authenticity and reliability before database entry. Upon study completion, paper case report forms will be stored in a locked cabinet. Investigators cannot modify data. All clinical trial results must undergo validation to ensure data reliability and confirm trial conclusions derive from original data. Corresponding data management measures exist throughout clinical trial and data processing phases.

Data collectors will use randomized number codes during data collection. After data collection concludes, the clinical monitor will unblind the primary blind of the randomized case report form, revealing the corresponding A/B codes (without disclosing the specific names of the A/B procedures). Statisticians use A/B codes instead of procedure names during statistical analysis. Following statistical analysis, outcome evaluators assess the efficacy and safety of the A/B procedures. After evaluation, the clinical monitor unmasks the secondary blind layer of the trial case randomization table, revealing whether the A/B intervention was acupuncture or sham acupuncture.

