## Discussion

3

Currently, many studies showed that obesity affects semen quality through multiple mechanisms (28, 29), which also leads to differences in the treatment of obese patients with asthenospermia compared to conventional idiopathic asthenospermia without obesity. Although clinical evidence supported the advantages of bariatric surgery in improving semen quality in obese men, some meta-analyses still indicated limited efficacy of bariatric surgery in this regard (30). Additionally, testosterone replacement therapy and hypoglycemic drugs are associated with poor patient compliance due to many adverse reactions (10). Therefore, exploring safe treatment pathways to meet patients’ fertility needs is still necessary. As an important component of TCM, acupuncture has gradually gained widespread application in metabolic and reproductive diseases in recent years. A lot of meta-analyses support the positive effects of acupuncture in losing weight (31, 32). While male infertility patients can also benefit from acupuncture treatment (33). We have designed this clinical trial focusing the comorbidity, and it would be the first study to confirm the efficacy and safety of acupuncture in the treatment of asthenospermia in obese men.

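### The aim to confirm safety claims more than 36 men per arm, sized on sperm motility alone, can deliver; it should be to describe safety

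*Protocol article*

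**What the plan says.** The Objective in the abstract is "This study aims to confirm the efficacy and safety of acupuncture in obese patients with asthenospermia". The Discussion says that "it would be the first study to confirm the efficacy and safety of acupuncture in the treatment of asthenospermia in obese men". The abstract's Results paragraph is more neutral but still treats safety as something the trial will settle: "This study is expected to demonstrate whether acupuncture is effective and safe in the treatment of asthenospermia in obese men".

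On size, section 2.1 states "A total of 72 participants will be recruited for this study, with 36 participants assigned to each group". Section 2.2.6 derives that number from the week 12 change in progressive sperm motility (PR) alone; safety does not enter.

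On the comparator, section 2.2.8 states "Both the acupuncture group and the sham acupuncture group underwent skin penetration, but the location and depth of the acupuncture will be different". Section 2.3.3 gives the sham arm the same retention time and treatment period as the acupuncture arm, at a depth of 2–3 mm, with a needle that "will be inserted at the acupoint without deqi sensation".

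On assessment, section 2.4.3 lists possible events and says that they will be recorded. Section 2.5.2 reports count data as frequency and percentage, and gives a general rule for such data: "For unordered categorical data, chi-square tests will be applied". Section 2.6 adds that "Following statistical analysis, outcome evaluators assess the efficacy and safety of the A/B procedures". No section names a safety hypothesis, a margin or a decision rule for adverse events.

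**The concern.** To confirm that a treatment is safe is to exclude harm above some level. That takes enough treated men to put a useful ceiling on the risk of each event, or a comparison able to show that the risk is not materially raised. This trial was sized for neither.

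The comparator limits what a contrast can mean. Where an event can follow any skin penetration, as with superficial bruising, local infection or fainting, both arms carry some of the risk. The difference between them then measures only what deeper, manipulated needling adds to shallow needling. It says nothing about the absolute risk of being needled.

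The safety sentence of the eventual report is at stake. With the aim worded as it is, few or no events among 36 men could be presented as confirmed safety. The primary efficacy result is not affected.

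**Working it through.** **Inputs.** 36 men per arm (sections 2.1 and 2.2.6); pilot changes in PR of 6.6 ± 4.2 and 3.2 ± 3.7, α = 0.025 one-tailed, 90% power, 20% loss (section 2.2.6). The article gives no adverse event rates, so every event rate below is an assumption, shown over a range.

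**1. The plan's own number, to see what it was built for.**
- Difference in means: 6.6 − 3.2 = 3.4. Common SD: √[(4.2² + 3.7²)/2] = √15.665 = 3.958.
- n per arm = 2 × (1.960 + 1.282)² × 15.665 / 3.4² = 28.5, so 29. Solving with the t distribution gives 29.5, so 30.
- 30 × 1.2 = 36 per arm, 72 in total.

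The stated figures reproduce from the PR inputs alone.

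**2. What zero events in 36 men would exclude.** The upper limit solves (1 − p)³⁶ = tail probability.
- One-sided 95%: 1 − 0.05^(1/36) = 8.0%.
- Two-sided 95%: 1 − 0.025^(1/36) = 9.7%.

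If the planned 20% loss occurred and only completers counted, 36 × 0.8 = 28.8, about 29 men, and the limits would be 9.8% and 11.9%.

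**3. Chance that a real harm is seen in nobody: (1 − p)³⁶.**

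| Assumed true risk per man | Probability of no event in 36 men |
|---|---|
| 1% | 0.99³⁶ = 70% |
| 2% | 0.98³⁶ = 48% |
| 5% | 0.95³⁶ = 16% |

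**4. What a comparison of the arms could resolve.** The half-width of an approximate 95% interval for the difference, with the same rate p in both arms, is 1.96 × √[2p(1 − p)/36].
- p = 5%: 10.1 percentage points.
- p = 10%: 13.9 percentage points.

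For 20% against 10%, the power of a two-sided 0.05 chi-square test with 36 per arm is about 22%, and 80% power would need 199 per arm.

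**5. What the contrast means.** If an event has the same risk in both arms, the expected difference is 0 whatever that risk is: at 20% in both, about 36 × 0.20 = 7.2 men per arm would have the event, with no expected difference. The per-arm percentage would show this risk; the contrast would not.

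**The case against.** The strongest reply is that the article never sets the trap. A reader might infer from sections 2.5.2 and 2.6 together that a null chi-square test of A against B will be reported as confirmed safety. The documents do not support that. Section 2.6 describes a blinded assessment of coded procedures, with no test or decision rule, and the chi-square sentence in section 2.5.2 is general and not tied to adverse events. This part of the reply stands.

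A reader might also infer that the penetrating sham by itself makes safety unassessable because it cancels the harms of needling. That goes too far. Only the difference cancels, and only for harms equally likely in both arms. Needle length, depth and manipulation differ (sections 2.3.2 and 2.3.3), so harms tied to them do not cancel. Absolute risk also remains visible, because section 2.5.2 already reports counts and percentages. This stands too.

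Third, low precision for harms is common in trials sized on efficacy, and interval methods are often left to an analysis plan. That is fair as far as methods go. It does not rescue the wording, because no analysis plan can make 36 treated men confirm safety, and the claim is printed in the Objective and again in the Discussion.

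Two further criticisms are not pressed. Replacing chi-square by Fisher's exact test is not needed: by enumeration with 36 per arm, the uncorrected chi-square test has a type I error of about 1.5% to 5.8% for event rates of 3% to 10%, while Fisher's test lowers the power for 20% against 10% from 22% to 14%. And nothing in the article suggests that intended deqi sensation will be coded as an adverse event.

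**Conclusion.** The point holds as one about an overstated aim. The article promises to confirm safety, and a trial sized on PR with 36 men per arm cannot do so. A clean record in the acupuncture arm would leave a true risk of up to about 8.0% (one-sided) or 9.7% (two-sided) for any given event, and a 2% harm would go unseen 48% of the time. The main reason is precision. The penetrating sham is a secondary limit, since a contrast with it shows only the excess over shallow needling.

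The limits assume 36 assessed men with independent outcomes and one event type at a time; fewer assessed men would widen them. The 2% and other event rates are illustrative. Common reactions can still be described usefully, and nothing here bears on the efficacy analysis.

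**What to change.** - In the Objective of the abstract and in the Discussion, replace the claim to confirm safety with an aim to describe it. Align the abstract's Results paragraph, so that it no longer expects the trial to show whether acupuncture is safe.
- In section 2.5.2, add exact 95% confidence intervals to the number and percentage of men with each adverse event, within each arm.
- In the same section, state that the absence of a difference from a penetrating sham will not be read as evidence of safety, and that any contrast estimates only the excess over shallow needling.

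No change of significance test is needed. The cost is a few sentences and a more modest safety claim, with no new patients or data.

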**Methods:**

In our randomized controlled trial, 72 patients will be randomly assigned (1:1) to receive either acupuncture treatment or sham acupuncture treatment. Each group will receive treatment two times weekly for twelve weeks with another twelve weeks for follow-up. The primary outcome is the progressive sperm motility (PR). And the secondary outcomes include PR plus non-progressive sperm motility, sperm concentration, semen volume, sperm morphology, body mass index, waist-to-hip ratio, and body fat percentage. We will also evaluate adverse events that occur during the acupuncture process.

**Results:**

This study is expected to demonstrate whether acupuncture is effective and safe in the treatment of asthenospermia in obese men.

**Conclusion:**

The research findings will firstly provide new therapeutic evidence in treating asthenospermia of obese men and offer an alternative treatment options for improving the fertility of obese men.

**Study protocol registration:**

https://itmctr.ccebtcm.org.cn, identifier ITMCTR2025002025.

## Introduction

1

Obesity is a critical global health issue affecting over one billion people (1). It is linked to a lot of comorbidities impacting every organ system and doubles annual medical costs compared to individuals with normal weight in adults (2, 3). The global rise in obesity stems from interconnected factors, primarily characterized by high-calorie junk food with excess fat and sugars, lack of enough physical activity and other unhealthy lifestyles such as sleep deprivation, smoking, and excessive drinking (4). In recent years, the impact of obesity on male reproductive health has been extensively studied. Clinical evidence indicated a dose-response relationship between increasing body mass index (BMI) and subfertility (5, 6). Hammiche et al. (7) reported that overweight was negatively associated with the percentage of progressive motility type A (*P* = 0.036) and positively associated with the percentage of immotility type C (*P* = 0.002). Ramaraju et al. (8) reviewed computer-aided sperm analysis data from 1,285 men and found that obesity was associated with lower progressive motility and total motility. Additionally, obese men were more likely to have asthenospermia and oligospermia (8). The mechanism by which obesity affects male semen quality may be related to aggravated oxidative stress, sperm DNA damage, decreased mitochondrial activity, and epigenetic changes (9).

The treatment of asthenospermia in obese men includes lifestyle interventions, medication, and weight loss surgery (10). Physical exercise may be generally associated with improved markers of male fertility, though outcomes may depend on the form and intensity of activity (11). Metformin and GLP-1 agonists exhibit ambiguous impacts, with evidence pointing to both positive and negative influences on reproductive health in men (12). Also, surgical approaches such as bariatric surgery are beneficial for correcting hormonal imbalances, yet their effects on semen parameters remain inconsistent (13). Therefore, identifying effective interventions that concurrently mitigate obesity and improve semen quality remains a central challenge in enhancing male fertility. Acupuncture has been widely used in some Asian countries. In previous reviews, we have analyzed the role of acupuncture in andrological diseases, and its mechanism included regulating sex hormone levels, modulating the autonomic nervous system, and improving oxidative stress (14, 15). Acupuncture can also improve the semen quality through enhancing the function of cation channels in spermatozoa, then leading to increased calcium ion influx and improved sperm motility (16). Although some studies have shown that acupuncture can improve sperm motility and body mass index (BMI) in men (17, 18), its effect on semen quality in obese men remains unknown. Therefore, we designed this randomized controlled trial to evaluate the impact of acupuncture on semen quality in obese men with asthenospermia.

## Materials and methods

2

### Study design and settings

2.1

Our study is a 1:1 randomized controlled trial with two parallel groups and will be reported in accordance with the Standards for Reporting Interventions in Clinical Trials of Acupuncture and the SPIRIT 2013 Statement (19, 20). A total of 72 participants will be recruited for this study, with 36 participants assigned to each group. All participants will receive a course of acupuncture treatment after being informed about the study, risks, and benefits, and after signing an informed consent form. The trial flow chart and time point of the assessment are shown in Figure 1 and Table 1.

**FIGURE 1 F1:**
[figure not shown]
Study flowchart.

**TABLE 1 T1:** A process chart of the trial.

Timepoint	Enrollment	Allocation	Treatment phase			Follow-up phase	
	Week-1	Week 0	Week 4	Week 8	Week 12	Week 18	Week 24
**Enrollment**							
Inclusion/exclusion criteria	X						
Informed consent	X						
Physical examination	X						
Randomization and allocation	X						
Demographic characteristics	X						
Allocation		X					
**Intervention**							
Acupuncture			X	X	X	X	X
Sham acupuncture			X	X	X	X	X
**Assessment**							
PR		X	X	X	X	X	X
PR plus NP		X	X	X	X	X	X
Sperm concentration		X	X	X	X	X	X
Semen volume		X	X	X	X	X	X
Sperm morphology		X	X	X	X	X	X
BMI		X	X	X	X	X	X
waist-to-hip ratio		X	X	X	X	X	X
Body fat percentage		X	X	X	X	X	X
Adverse events			X	X	X	X	X

BMI, body mass index; PR, progressive sperm motility; NP, non-progressive sperm motility.

### Study participants

2.2

#### Recruitment strategy

2.2.1

We will screen and recruit participants from November 2025 to October 2026 at the Department of Andrology, Xiyuan Hospital, China Academy of Chinese Medicine Sciences. Our researchers will be systematically trained and fully informed of the trial procedures. Informed consent will be obtained from participants prior to enrollment. Participation will be entirely voluntary, and participants will have the right to withdraw from the trial at any time without penalty.

#### Diagnostic criteria

2.2.2

Diagnostic criteria for asthenospermia and obesity were established in accordance with the World Health Organization Manual for the Examination and Processing of Human Semen (5th Edition) and the “Health Industry Standard of the People’s Republic of China–Measurement of Adult Body Weight” (Standard No. WS/T428-2013) (21, 22). All participants must meet both the diagnostic criteria for asthenospermia and obesity simultaneously.

Diagnostic criteria for asthenospermia: Based on two or more semen analyses, the percentage of progressive motility spermatozoa in the semen is below the reference lower limit of 32%.

Diagnostic criteria for obesity: Based on body mass index (BMI = weight/height^2^), the BMI ≥ 28 kg/m^2^ is defined as obesity.

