#### Sample size consideration

2.2.6

This trial employed a randomized, double-blind, parallel-group design. Sample size calculations were based on the primary efficacy indicators, estimated as the change in PR from baseline at week 12 of treatment. Based on our preclinical pilot study, acupuncture treatment for asthenozoospermia yielded a mean percentage change of 6.6 ± 4.2, while sham acupuncture treatment showed a mean change of 3.2 ± 3.7. With α = 0.025 (one-tailed) and β = 0.1 (90% power), the critical value was estimated as δ = 5% (1/5 of the mean change). With a 1:1 trial-to-control ratio, each group requires 30 participants. Strict quality control during the trial will limit the loss to follow-up rate to 20%, resulting in a total study sample of 72 participants, and finally 36 in the trial group and 36 in the control group.

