#### Primary outcome measure

2.4.1

Progressive sperm motility (PR) refers to the proportion of sperm in semen that can move in a straight line or with a larger radius, which is an important indicator for assessing sperm motility. We will assess the PR at week 12 as the primary outcome.

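### The PR readings that qualify each man for entry could sharpen the week-12 comparison as a second covariate; this is a cheap precision gain, not an error

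*Protocol article*

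**What the plan says.** Section 2.2.2 (Diagnostic criteria) sets the entry threshold: "Based on two or more semen analyses, the percentage of progressive motility spermatozoa in the semen is below the reference lower limit of 32" per cent. Section 2.2.3 makes meeting it an inclusion criterion.

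Table 1 marks PR once before treatment, at week 0, and not in the Week-1 enrollment column. It then marks PR at weeks 4, 8, 12, 18 and 24.

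Section 2.2.6 sizes the trial on PR "estimated as the change in PR from baseline at week 12 of treatment". Section 2.4.1 words the endpoint differently: "We will assess the PR at week 12 as the primary outcome".

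Section 2.5.2 (Data analysis) lists rank-sum tests, chi-square tests and repeated measures ANOVA. It names no covariate. The article does not define baseline PR, state how many samples the week-0 assessment uses, or say whether the qualifying values are kept as trial data.

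**The concern.** PR readings taken before randomisation cannot be affected by the allocated arm. Using them as covariates therefore leaves the comparison between arms unbiased and removes part of the between-man variation from it. At least two such readings exist for each man, yet the article gives them no role after eligibility.

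What is at stake is precision in a trial with about 29 to 36 men per arm at week 12. Timing matters as well. Section 2.2.1 has recruitment running from November 2025 to October 2026. A later analysis plan can add a covariate only if its values and dates were captured at entry.

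**Working it through.** **Inputs from section 2.2.6.** "acupuncture treatment for asthenozoospermia yielded a mean percentage change of 6.6 ± 4.2"; "sham acupuncture treatment showed a mean change of 3.2 ± 3.7"; one-sided α of 0.025; 90% power; and "With a 1:1 trial-to-control ratio, each group requires 30 participants".

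**Step 1: reproduce the plan's figure.**
- Difference: 6.6 − 3.2 = 3.4.
- Pooled SD: √[(4.2² + 3.7²)/2] = 3.958.
- n per group = 2 × (3.958 × (1.960 + 1.282)/3.4)² = 28.5, so 29 by the normal approximation and 30 with the noncentral t.
- The stated 30 holds, with t-based power of 90.5%.
- After the planned 20% loss, 36 × 0.8 = 28.8 men per arm remain. At 29 per arm the t-based power is 89.5%. That small dip comes from how the loss was allowed for, not from how baseline is handled.

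**Step 2: residual variance with and without the qualifying readings.** Assumptions, none of them in the article: every PR reading has the same variance s², any two readings on one man have correlation ρ, and the two qualifying readings are separate from week 0.
- Change from week 0: 2s²(1 − ρ).
- ANCOVA on week-0 PR: s²(1 − ρ²), which is (1 + ρ)/2 of the change-score variance.
- ANCOVA on week-0 PR plus the mean of two qualifying readings: s²[1 − 3ρ²/(1 + 2ρ)].
- Ratio of the third to the second: (1 + 3ρ)/[(1 + 2ρ)(1 + ρ)].

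| ρ | ratio | further cut | n per group for 90% power: change / ANCOVA on week 0 / plus qualifying mean |
|---|---|---|---|
| 0.3 | 1.9/(1.6 × 1.3) = 0.913 | 9% | 29 / 19 / 17 |
| 0.5 | 2.5/(2.0 × 1.5) = 0.833 | 17% | 29 / 22 / 18 |
| 0.7 | 3.1/(2.4 × 1.7) = 0.760 | 24% | 29 / 25 / 19 |

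The n columns use the normal approximation and hold the pilot change SD at 3.958. They only express the gain on a familiar scale and are not a case for a smaller trial.

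If week 0 is itself one of the two qualifying readings, only one extra reading is available. The ratio is then (1 + 2ρ)/(1 + ρ)²: 1.6/1.69 = 0.947, 2/2.25 = 0.889 and 2.4/2.89 = 0.830, a cut of 5% to 17%.

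**Step 3: allow for selection.** Requiring PR below 32% narrows the range of the qualifying readings and weakens them as predictors. A simulation took total SD 12, population mean 28 or 35, both qualifying readings below 32, and ρ from 0.3 to 0.7. The further cut was about 3% to 16% with two extra readings, and from about 2% when week 0 was one of the two. An SD of 12 implies a change SD of about 9 to 14, far above the pilot's 4. With inputs matched to the pilot SD and a mean well below 32, selection matters little and the cut approaches the 24% in the table. Hence the range of 2% to 24%.

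**Step 4: the price of the covariate.** With 58 men analysed, an uninformative second covariate inflates the variance of the treatment effect by about 54/53, or 2%. At the bottom of the range the net gain is therefore nil.

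**Step 5: why not average the readings into baseline.** Readings required to be low will on average rise on repetition. In an assumed setting (mean 25, SD 8), taking the mean of two qualifying readings as baseline raised the apparent within-arm change by about 1.1 points at ρ = 0.5 and 0.6 points at ρ = 0.7. A separate week-0 reading gave no shift. The shift cancels between arms, but it is not small beside the pilot sham change of 3.2.

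**The case against.** The strongest reply is that nothing here is wrong. An article may leave the derivation of baseline and the choice of covariates to the full protocol or analysis plan. The diagnostic rule is sound as written and conflicts with no other section, and the sample size reproduces. If the pilot also used one baseline reading, its SDs already contain that noise. All of this stands, which is why the point is offered only as an improvement.

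A reader might infer three stronger things, and the documents support none of them.
- That baseline PR is a single reading: one mark in a visit table shows that an assessment takes place, not how many samples it uses.
- That the plan itself regards one reading as too variable: section 2.2.2 says its criteria follow a WHO manual and a national standard, and says nothing about within-man variability.
- That averaging three readings into baseline would lift power from 89.5% to between 92% and 98%: this range supposes that 25% to 100% of the change variance is sampling noise, which the article does not show. It also describes a change-score analysis, whereas the primary outcome is worded as PR at week 12.

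It is also fair to say that most of the available gain comes from adjusting for week-0 PR at all. The table shows this, and the qualifying readings add to it. Their comparability is unknown, so the addition could be zero.

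**Conclusion.** The point holds as a low-cost gain in precision. The article shows that at least two pre-treatment PR values exist per man, and it describes no use of them beyond eligibility. It does not say that they are discarded.

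Using their mean as a second covariate would cut residual variance by a further 2% to 24% beyond adjustment for week-0 PR, less about 2% for the lost degree of freedom. That range rests on equal variances, a common correlation of 0.3 to 0.7, and qualifying readings comparable with those in the trial. If the readings are old or from another laboratory, the gain may vanish. No bias and no power shortfall follows from leaving the plan as it is.

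**What to change.** 1. Record the PR value, date and laboratory of every qualifying semen analysis in the case report form, including for men already enrolled.
2. State which sample or samples make up week-0 PR, and whether week 0 can count towards eligibility.
3. Pre-specify the primary comparison as an ANCOVA of week-12 PR on arm, with week-0 PR as one covariate and the mean of the qualifying readings as a second. Leave week 0 out of that mean if it is one of the qualifying readings. A separate coefficient lets the data give the qualifying readings little weight if they are not comparable.
4. Do not average the qualifying readings into the baseline for change. Report within-arm change descriptively from week 0 only, and note that it too is selected low if week 0 counts towards eligibility.

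The cost is a few form fields, one analysis sentence and one degree of freedom for the second covariate. No extra samples, visits or participants are needed. The downside is little or no gain if the qualifying readings prove not to be comparable.
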